## Abstract

**Introduction:**

Surgical repair of congenital heart defects often requires the use of cardiopulmonary bypass (CPB) and cardioplegic arrest. Cardioplegia is used during cardiac surgery requiring CPB to keep the heart still and to reduce myocardial damage as a result of ischaemia–reperfusion injury. Cold cardioplegia is the prevalent method of myocardial protection in paediatric patients; however, warm cardioplegia is used as part of usual care throughout the UK in adults. We aim to provide evidence to support the use of warm versus cold blood cardioplegia on clinical and biochemical outcomes during and after paediatric congenital heart surgery.

**Methods and analysis:**

We are conducting a single-centre randomised controlled trial in paediatric patients undergoing operations requiring CPB and cardioplegic arrest at the Bristol Royal Hospital for Children. We will randomise participants in a 1:1 ratio to receive either ‘cold-blood cardioplegia’ or ‘warm-blood cardioplegia’. The primary outcome will be the difference between groups with respect to Troponin T levels over the first 48 postoperative hours. Secondary outcomes will include measures of cardiac function; renal function; cerebral function; arrythmias during and postoperative hours; postoperative blood loss in the first 12 hours; vasoactive-inotrope score in the first 48 hours; intubation time; chest and wound infections; time from return from theatre until fit for discharge; length of postoperative hospital stay; all-cause mortality to 3 months postoperative; myocardial injury at the molecular and cellular level.

**Ethics and dissemination:**

This trial has been approved by the London – Central Research Ethics Committee. Findings will be disseminated to the academic community through peer-reviewed publications and presentation at national and international meetings. Patients will be informed of the results through patient organisations and newsletters to participants.

**Trial registration number:**

ISRCTN13467772; Pre-results.

Strengths and limitations of this studyThis is the first randomised controlled trial to compare warm-blood cardioplegia with cold blood cardioplegia in the paediatric cardiac population. Previous research has compared cold crystalloid cardioplegia with warm-blood cardioplegia, so we hope to provide evidence to support the use of one type of cardioplegia.We are incorporating the Trials Engagement in Children and Adolescents Study Within A Trial. We will use trial data to answer multiple objectives, informing evidence-based decisions in trials.We have a broad eligibility criterion, so the trial results should be generalisable to a large population, including both simple and complex cardiac surgery procedures.Stratification will be used to ensure that surgical complexity is balanced across the two treatment groups.The primary outcome and majority of secondary outcomes are objective. Staff providing postoperative care will be blinded to the treatment allocation to minimise performance and detection bias.

## Introduction

### Background

Surgical repair of congenital heart defects often requires the use of cardiopulmonary bypass (CPB). CPB is a technique that temporarily takes over the function of the heart and lungs (pumping blood and oxygen through the body) and occasionally involves stopping the heart during surgery. In cases where the heart must be stopped, use of CPB is associated with complications such as myocardial damage as a result of ischaemia–reperfusion injury (IRI; myocardial damage occurs when the blood supply returns to the heart after a period of restricted blood flow/ischaemia). Cardioplegia is used to stop the heart and for myocardial protection during cardiac surgery requiring CPB. Recovery and outcome statistics show a continued need to improve myocardial protection: myocardial damage can prolong hospital stay and result in delayed myocardial fibrosis^1^; and myocardial damage with low cardiac output is the most common cause of morbidity after surgical repair.^1–4^

Currently, there is wide variation in the use of cardioplegia in congenital cardiac surgery. Hypothermic cardioplegia solution is the prevalent method of myocardial protection in paediatric patients, however, there is wide variation in practice.^5 6^ Cold cardioplegia is used to lower myocardial oxygen demands and the risk of IRI. However, intermittent warm-blood cardioplegia (IWBC) is considered to be an effective method of myocardial protection in adults undergoing surgical repair and is used in usual practise in the UK. The main benefits can be summarised as: (1) improved oxygen supply and reduced myocardial oedema; (2) more practical, because a simple electrically driven pump can be used instead of more complex cooling devices; and (3) cost-effective, because the expenses for cooling devices are not required.^7^

There have been a series of clinical and experimental studies confirming the effectiveness of IWBC compared with cold-blood cardioplegia (CBC) in adults.^8 9^

Findings from the adult cardiac surgery field cannot be applied to paediatric cardiac surgery patients. The first studies looking at the effectiveness of IWBC in children undergoing cardiac surgery have demonstrated that IWBC is a safe and effective strategy of myocardial protection. However, the studies have been limited to a retrospective comparison of 1400 patients who underwent cardiac surgery using IWBC with 950 patients treated with intermittent cold-blood
cardioplegia (ICBC)^10^; and a small single centre randomised
controlled trial (RCT) which compared cold crystalloid cardioplegia with IWBC.^11^

We would like to take this a step further and provide evidence to support the use of one type of cardioplegia^12^ by investigating the effects of warm versus CBC on clinical and biochemical outcomes after paediatric congenital heart surgery.

#### Embedded TRECA Study Within A Trial (SWAT)

The Thermic-3 trial is embedding the Trials Engagement in Children and Adolescents (TRECA) SWAT.^13^ This SWAT is investigating a novel method for recruitment to see whether providing children and their families with information about a trial through multimedia information (MMI) resources impacts on recruitment and retention rates and the quality of decision-making about trial participation. The MMI resources are websites with text, images, animations and videos about the Thermic-3 trial. They have been developed by TRECA in conjunction with the Thermic-3 trial team.

### Aims and objectives

The main aim of the Thermic-3 trial is to compare IWBC with ICBC in paediatric patients undergoing open heart surgery. The objectives are to estimate the differences between groups with respect to the following:

Myocardial damage using serum Troponin T (cTnT) levels (primary outcome).A range of clinical postsurgical outcomes: cardiac function; cardiac index; renal function; arrythmias intraoperatively and postoperatively; postoperative blood loss in the first 12 hours; vasoactive-inotrope score (VIS) in the first 48 hours; intubation time; chest and wound infections; time from return from theatre until fit for discharge from paediatric intensive care unit; length of postoperative hospital stay; all-cause mortality to 3 months postsurgery; myocardial injury at the molecular and cellular level (secondary outcomes).

## Methods and analysis

### Trial design and population

The Thermic-3 trial is a single-centre RCT comparing warm-blood cardioplegia (WBC) with CBC. We will recruit patients being referred for cardiac surgery requiring CPB and cardioplegia arrest at the Bristol Royal Hospital for Children (BRHC). Thermic-3 recruitment began in May 2018. The first patient was randomised on 2 June 2018. We anticipate that recruitment will be completed within 24 months.

### Eligibility criteria

Patients will be eligible if they:

Are undergoing a congenital heart operation requiring CPB and cardioplegic arrest at the BRHC (age range 0–18 years old).

Patients will be ineligible if they:

Weigh <3 kg.Require an emergency operation (patient with haemodynamic instability who require immediate surgical intervention defined as operation within 24 hours of admission).Require secundum atrial septal defect repair as an isolated procedure.Are judged preoperatively by the surgeon to require deep hypothermic circulatory arrest (eg, aortic arch repair, repair of total anomalous pulmonary venous drainage, Norwood procedure).Are judged pre-operatively by the surgeon to require deep hypothermic CPB.Have a procedure that is judged by the surgeon to be preoperatively too complex. This could be procedure related or patient related (eg, complex tailor-made surgery; necrotising enterocolitis; preoperative brain haemorrhage; or generalised bleeding state/ongoing major bleeding).Are of consenting/assenting age, however lacking capacity to consent/assent.Are under the care of social services and/or the parent/guardian is unavailable for consent.

### Patient approach and consent

Potential trial participants will be identified from theatre and clinic lists. Prior to approach about the Thermic-3 trial, potential patients will be randomised (1:1:1) to one of the three TRECA SWAT groups: patient information leaflet (PIL), MMI or both PIL and MMI.^13^ Parents/guardians will be given either a PIL, MMI or both PIL and MMI. Patients aged over 7 years old will also be provided with a PIL, MMI or both PIL and MMI suitable to their age group (7–10 years, 11–15 years or 16 years and over). If the study information is posted, parents/guardians or patients will also receive an invitation letter. All invitation letters, PILs and MMI have been approved by the Research Ethics Committee (REC). The MMI will be provided in the same way as the PILs. For example, the research nurse will be able to show the family the MMI on a tablet at the hospital. All parents/guardians and patients allocated to receive MMI will receive the link to the MMI on a laminated card so that they can review the MMI at home, either on a computer, tablet or smart phone.

Most patients will have at least 24 hours to consider whether to participate. In a few cases, this time interval may be less, for example, patients admitted for an operation without prior notification. Despite short notice, it is important to include these patients for the applicability of the trial findings. Written informed consent/assent for Thermic-3 will be obtained from the patient and/or their parent/guardian (where appropriate) prior to inclusion. Online supplemental files 1–3 show the consent/assent forms for the Thermic-3 trial. Figure 1 shows the expected patient pathway for the Thermic-3 trial.

10.1136/bmjopen-2020-036974.supp1Supplementary data

10.1136/bmjopen-2020-036974.supp2Supplementary data

10.1136/bmjopen-2020-036974.supp3Supplementary data

**Figure 1 F1:**
[figure not shown]
Trial schema showing the recruitment pathway with the number of patients to be recruited, anticipated eligibility and recruitment rates.

### Trial interventions

Eligible patients who give consent will be randomised to receive one of the following:

WBC: blood cardioplegia at the same temperature as the body (≥34°C).CBC: blood cardioplegia at 4°C–6°C.

For both groups, route of cardioplegia infusion will usually be into the aortic root, or selectively into the right or left coronary artery. The cardioplegia delivery methods will differ between the two groups. First, the temperature of the cardioplegia will be delivered as per the patient’s randomisation allocation (warm or cold). Second, the delivery for the cardioplegia will differ between groups. For example, the concentration of the cardioplegia and frequency of infusion and reinjection rates differ slightly between groups. Details of the differences are described below. For the purpose of the trial, the two different techniques are abbreviated as ‘warm’ and ‘cold’ cardioplegia. The cardioplegia concentrations are provided in online supplemental file 4.

10.1136/bmjopen-2020-036974.supp4Supplementary data

#### Warm cardioplegia

The cardioplegic solution will be prepared by mixing a patient’s own blood with sterile concentrate for cardioplegia infusion to achieve a final composition of 20 mM K^+^ and 5mM Mg^2+^.^10^ Blood will be withdrawn directly from the oxygenator using a pump and then re-infused at ≥34°C.

Initial infusion and reinjection rates will be calculated according to the patient’s body surface area. The flow will be equal to 1–1.5 times the physiologic coronary flow (estimated as 5% of the cardiac output). The arresting dose of cardioplegia will be given for 1 min following electromechanical arrest of the heart. Reinjections at two-thirds of the initial speed of injection will be performed for 1 min every 15 min during aortic cross-clamping.

#### Cold cardioplegia

Cold blood (4°C–6°C) high strength cardioplegic solution will be used for myocardial preservation. This will be mixed with the patients’ blood withdrawn from the CPB circuit to give a ratio of 4 parts blood to 1-part cardioplegia solution. The mixture will be administered via a cardioplegia module that cools the solution to a temperature of approximately 4°C.

The induction dose will be 110 mL/min/m^2^, antegradely for 4 min, with a maintenance dose of 110 mL/min/m^2^ for 2 min at 20/30 min intervals.

The CPB temperature will be at the discretion of the operating surgeon. This will allow a degree of adaptation depending on the operation type. Temperature data will be collected throughout the operation to have a good understanding of the temperature variation on CPB.

### Randomisation

Eligibility will be confirmed, and consent given before randomisation takes place. The sequence of random allocations will be prepared in advance by a statistician using a computer by block randomisation method, with varying block sizes. Randomisation will take place via a secure password-protected database. Randomisation allocation will be concealed from all clinical and research personnel until a patient has been recruited and registered onto the trial database. Participants will then be randomly assigned in a 1:1 ratio and will be stratified by surgical complexity (Risk Adjustment for Congenital Heart Surgery (RACHS) score <3; RACHS score ≥3).

Randomisation within Thermic-3 will take place as close to the start of surgery as possible. If a participant’s surgery is unexpectedly rescheduled, the trial number and randomisation allocation will be retained.

### Trial outcomes

The primary outcome will be cTnT levels over the first 48 postoperative hours (measured using Roche Elecsys Troponin T-hs (TnT-hs) assay, the routine analysis method used by the recruiting hospital). cTnT will be measured presurgery and at 2 hours, 6 hours, 24 hours and 48 hours post cross-clamp (XC) removal.

The secondary outcomes include the following:

Cardiac function assessed by indirect measures of cardiac output (central venous saturations (ScvO_2_), arterial saturations, base deficit and blood lactate) will also be recorded. ScvO_2_ will be measured via venous blood aspirated from the central venous catheter, up to 48 hours after XC removal. Arterial saturations, base deficit and lactate will be measured in arterial blood via sampling from the peripheral arterial cannula.Routine blood gas and blood samples (pH, PO_2_, PCO_2_, base excess, lactate, C reactive protein, haemoglobin, haematocrit, white cell count and alanine aminotransferase).Measures of renal function (urinary albumin, urinary creatinine, retinal binding protein, N-acetyl-β-glucosaminidase and neutrophil gelatinase-associated lipocalin).Arrhythmias including atrial fibrillation/flutter, ventricular tachycardia, ventricular fibrillation, nodal, junctional ectopic tachycardia (JET) or atrioventricular (AV) block.Postoperative blood loss in the first 12 hours.New onset of arrhythmia postoperatively (either supraventricular tachycardia/atrial fibrillation or ventricular fibrillation/ventricular tachycardia, JET or heart block).VIS over the first 48 hours after admission to paediatric intensive care unit (PICU).^14^Postoperative intubation time in hours (including instances of reintubation).Time from return from theatre until fit for transfer to the ward/high dependency unit (HDU) from the PICU. Fit for discharge to the ward/HDU will reflect current ward/HDU admission criteria.Chest and wound infections.All-cause mortality to 3 months postsurgery.Length of postoperative hospital stay in days (from surgery to discharge from hospital).Myocardial injury at the molecular and cellular level (eg, transcriptomics, proteomics and metabolomics)^15–17^ measured in samples considered clinical waste. Where sufficient waste tissue, plasma and serum are available, metabonomics, proteonomics and transcriptomics, microRNA and isolated progenitor cells will be investigated. It will be assessed whether the isolated progenitor cells have similar regenerative capacity, in patients subjected to different surgical protocols.

### Data collection

The schedule of data collection is shown in table 1. Data will be collected from medical notes and hospital records, entered onto a bespoke database and stored on a secure server.

**Table 1 T1:** Schedule of data collection

Data items and samples collected	Preoperative	Postoperative											Subsequent days up to hospital discharge	Hospital discharge	3 Months postoperative
		Presurgery	Start of CPB	10 min post CPB	XC removal	XC + 1 hour	XC + 2 hours	XC + 4 hours	XC + 6 hours	XC + 12 hours	XC + 24 hours	XC + 48 hours			
Screening and consent data	**✓**														
Baseline data (patient demographics, medical history, medications)	✓														
Randomisation allocation	✓														
Routine blood gases		**✓**			**✓**	**✓**		**✓**			**✓**	**✓**			
Routine blood samples		**✓**						**✓***				**✓**	**✓**		
Blood for Troponin T		**✓**					**✓**		**✓**		**✓**	**✓**			
Central venous saturations						**✓**†	**✓**†	**✓**†	**✓**†	**✓**†	**✓**†	**✓**†			
Arterial saturations, base deficit and lactate		**✓** (induction)				**✓**		**✓**		**✓**	**✓**				
Urinary albumin and creatinine, RBP, NAG and N-GAL		**✓**						**✓**			**✓**	**✓**			
Operative details‡		**✓**	**✓**	**✓**	**✓**										
Waste heart tissue (if available)					**✓**										
Clinical outcomes														**✓**	
Safety data postdischarge															**✓**

*Routine bloods taken on admission to PICU.

†Several ScvO_2_ readings will be taken from XC removal until XC+ 48 hours.

‡Operative details are recorded on XC removal and chest closure.

CPB, cardiopulmonary bypass; NAG, N-acetyl-β-glucosaminidase; N-GAL, neutrophil gelatinase-associated lipocalin; PICU, paediatric intensive care unit; RBP, retinal binding protein; XC, cross-clamp.

### Blinding

Staff providing postoperative care will be blinded to the participant’s treatment allocation. Documentation containing the treatment allocation (eg, perfusion charts) will be placed in a sealed envelope within the medical notes. Any member of staff accessing the documents will be asked to record their name and the reason for accessing the documentation.

### Sample size calculation

The sample size calculation is based on cTnT levels which were measured in a previous RCT.^16^ The data were log normal with correlations between pre and post measures of about 0.3 and between successive post measures of about 0.5. Given these correlations and four repeated postoperative measures, a sample size of 94 patients (47 per group) is sufficient to detect a standardised difference of 0.46 SDs (moderate effect size) in cTnT with 80% power and 5% significance (two-tailed), allowing for up to 15% missing data for cTnT.

### Statistical analysis

The trial will be analysed on an intention-to-treat basis, that is, outcomes will be analysed according to the treatment allocation, following a prespecified analysis plan. Any non-adherence to the allocated group will be documented. The primary outcome (cTnT levels over the first 48 postoperative hours) will be analysed using a longitudinal mixed-regression model, which allows for unbalanced data. All secondary outcomes will yield either binary, quantitative, time to event or longitudinal data, and will be analysed using linear regression (quantitative outcomes) or survival methods (time to event outcomes). Binary secondary outcomes will be described but not formally compared. Analyses will be adjusted for baseline values (where measured), and surgical complexity (stratification factor). Differences between the two groups will be reported as effect sizes with 95% CIs.

The transcriptomics data will be analysed using specialised software. Gene expression profiles will be determined, then the biological function of the identified genes will be established in order to generate hypotheses about their role. The signalling pathway to which these genes belong will be explored. The selection of important candidate genes will be validated.

It is expected that low numbers of adverse events are likely to be experienced by trial participants, based on our previous trials and due to the relatively small sample size and short follow-up period. For this reason the trial will not have an independent Data Monitoring and Safety Committee, but will be overseen by the Steering Group established to provide oversight of all studies supported by the National Institute for Health Research Bristol Cardiovascular Biomedical Research Centre Cardiovascular theme.

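### Binary secondary outcomes have no planned estimate or interval, although the objective is to estimate group differences in outcomes that include arrhythmias and infections

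*Protocol article*

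**What the plan says.** Three statements in the protocol article bear on this point.

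- **Aims and objectives** opens its list with "The objectives are to estimate the differences between groups with respect to the following". The clinical outcomes under it include "arrythmias intraoperatively and postoperatively; postoperative blood loss in the first 12 hours", chest and wound infections, and, at the end, "all-cause mortality to 3 months postsurgery; myocardial injury at the molecular and cellular level (secondary outcomes". No outcome is exempted.
- **Statistical analysis** gives methods for the secondary outcomes: they "will be analysed using linear regression (quantitative outcomes) or survival methods (time to event outcomes". The next sentence reads "Binary secondary outcomes will be described but not formally compared".
- **Statistical analysis**, two sentences further on: "Differences between the two groups will be reported as effect sizes with 95% CIs". This carries no stated exception.

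The article does not list which secondary outcomes are binary.

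**The concern.** The objective is worded as estimation, and the analysis rule for one class of outcomes does not deliver estimation. An analyst who follows the rule could properly produce event counts and percentages by arm and stop there. The trial would then have no stated difference, and no measure of its uncertainty, for outcomes that it set out to estimate.

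The primary outcome is a biomarker, while the abstract and background present the trial as evidence on clinical as well as biochemical outcomes. Arrhythmia and infection are among the results that clinicians will read directly. In a trial of this size, two similar percentages invite the conclusion that the techniques do not differ, and two dissimilar ones invite the conclusion that they do. An interval guards against both.

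**Working it through.** **1. The texts side by side**

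| Item | Objective | Analysis stated |
|---|---|---|
| Quantitative outcomes | Estimate difference | Linear regression |
| Time-to-event outcomes | Estimate difference | Survival methods |
| Binary outcomes | Estimate difference | Described; no estimator named |

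Only the last row has no route from objective to estimate. Classing arrhythmia and infection as binary is an inference, though a strong one. Mortality to 3 months could fall in the second or the third row.

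**2. The plan's own sample size**

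The Sample size calculation section says "a sample size of 94 patients (47 per group) is sufficient to detect a standardised difference of 0.46 SDs", "with 80% power and 5% significance (two-tailed), allowing for up to 15% missing data for cTnT". Inputs from that section: pre-post correlation 0.3, correlation between post measures 0.5, four post measures. Assuming a common correlation between all post measures, the variance factor for the baseline-adjusted mean is

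(1 + 3 × 0.5)/4 − 0.3² = 0.625 − 0.09 = 0.535.

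Per group: 2 × 0.535 × (1.96 + 0.842)² / 0.46² ≈ 39.7. Allowing for 15% missing: 39.7/0.85 ≈ 46.7, so 47. The stated figure reproduces. It concerns troponin only, and nothing in this point changes it.

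**3. What an interval would look like at 47 per group**

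The article gives no event rate for any binary outcome, so the rates below are assumptions, equal in both arms, with all 47 per group contributing. The approximate (Wald) half-width of the 95% CI for a risk difference is 1.96 × √(2p(1−p)/47).

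| Assumed rate p | Half-width (percentage points) |
|---|---|
| 5% | 8.8 |
| 10% | 12.1 |
| 20% | 16.2 |
| 30% | 18.5 |

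The Newcombe method, which is better suited to few events, gives:

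| Events per arm (of 47) | Half-width (percentage points) |
|---|---|
| 1 (2%) | 9.2 |
| 2 (4%) | 10.5 |
| 5 (11%) | 13.4 |
| 9 (19%) | 16.0 |
| 14 (30%) | 18.0 |

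As an illustration, 5 events against 9 is 10.6% against 19.1%. The difference is −8.5 points, with a Newcombe 95% CI from −23.2 to 6.3. The two percentages alone suggest a near-halving; the interval shows that the data are compatible with a difference in either direction.

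**4. Would tests be worthwhile?**

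With 47 per group and assumed rates, power of a two-sided 5% test is 8% for 2% against 4%, 15% for 5% against 10%, 27% for 10% against 20%, and 56% for 20% against 40%. This supports leaving out the tests. It is no reason to leave out the estimate.

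**The case against.** The strongest defence has four parts.

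**The sentence may only rule out tests.** Declining a formal comparison can mean no P value, which is compatible with a risk difference and its interval. Alternatively, the sentence on effect sizes and CIs may cover only the outcomes that are modelled. A reader might infer a flat contradiction within the Statistical analysis section; the text does not support that, because either reading removes it. Something remains all the same. Under the first reading the text does not say that an estimate will be given, and needs to. Under the second, binary outcomes have no estimate and the objective is unmet for them.

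**The affected outcomes are not listed.** A reader might infer that death will be given only as two percentages. The article does not establish this, since mortality to 3 months could be analysed with the survival methods it names. This part of the objection stands, so the point is firm only for arrhythmia and infection.

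**The detail may be in the analysis plan.** The article refers to a prespecified plan, which is not shown, and that plan may define what description includes. That is fair as far as it goes. The point, however, rests on a rule that the article itself states and that does not fit its own objective.

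**Description without testing is a legitimate choice.** The trial is sized on troponin and expects few adverse events. With counts and denominators by arm, any reader can also compute an unadjusted interval. Both statements are right, and they limit the importance of the point. They do not explain why the trial should leave its readers to compute a difference that it undertook to estimate.

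**Conclusion.** The point holds as a mismatch between the stated objective and the stated analysis rule. On the natural reading of the rule, arrhythmia and infection, and mortality if analysed as binary, have no planned estimate of difference and no interval. The fit with the sentence on 95% CIs is ambiguous. The decision not to test is defensible and should stay.

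On size: over assumed event rates of 5% to 30% with 47 per group, the approximate half-width is about 9 to 19 percentage points. This shows how imprecise these comparisons would be; it does not show that any conclusion would be wrong. Sample size and primary analysis are unaffected.

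A reader might also link this to the decision to have no independent data monitoring committee. That decision concerns oversight during the trial, which the article assigns to a Steering Group. It has no bearing on how results are reported at the end.

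**What to change.** Replace the sentence on binary outcomes with:

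> *Binary secondary outcomes will be reported as counts and percentages by group, with risk differences and 95% CIs (score or Newcombe method, combined across RACHS strata where events allow); no hypothesis tests will be made.*

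State in the same place which secondary outcomes are binary and, in particular, whether mortality is analysed as binary or time to event.

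The alternative is to restrict the objective and the sentence on 95% CIs to the outcomes that are formally compared. That would also make the document consistent, but it gives up part of the stated objective.

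The cost is one sentence in the protocol or analysis plan and a little programming. The only downside is that wide intervals become visible.

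### The stated covariate rule has no measure of body size or age in a 0–18-year population, which could cost precision, chiefly for 12-hour blood loss

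*Protocol article*

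**What the plan says.** All references are to the protocol article.

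- **Covariates (Statistical analysis):** "Analyses will be adjusted for baseline values (where measured), and surgical complexity (stratification factor". No other covariate is named. The section also says that the analysis follows a prespecified plan, which is not shown.
- **Population (Eligibility criteria):** the range is "age range 0–18 years old". Children under 3 kg are excluded, and there is no upper weight limit.
- **Stratification (Randomisation):** surgical complexity only, in two levels.
- **Blood loss (Trial outcomes):** the whole entry is "Postoperative blood loss in the first 12 hours". It gives no unit and no scaling to weight or body surface area.
- **Models (Statistical analysis):** secondary outcomes "will be analysed using linear regression (quantitative outcomes) or survival methods (time to event outcomes". The primary outcome, cTnT, "will be analysed using a longitudinal mixed-regression model, which allows for unbalanced data".
- **Data at hand (Data collection, Table 1):** "Baseline data (patient demographics, medical history, medications" are recorded before surgery. Under Trial interventions, cardioplegia delivery is scaled to body surface area in both arms, so body size is known for every child.

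**The concern.** The trial mixes infants of about 3 kg with adolescents. An outcome measured as a volume can be expected to vary with the size of the child, whatever the treatment does. Blood loss after surgery has no preoperative counterpart, so the baseline half of the rule gives it nothing, and a two-level complexity score is all that remains. Any variation due to size then becomes residual error, and a chance difference in age or weight between two arms of 47 is not adjusted for in the estimate.

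For the primary outcome the rule does supply a baseline value, but the Sample size calculation section puts its correlation with later values at only about 0.3. There may be room for another prognostic covariate. At stake is precision that could be had from data already collected. A covariate added only after an imbalance has been seen would be post hoc, so the decision belongs before unblinding.

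**Working it through.** **1. The plan's own figure.** Inputs from Sample size calculation: four postoperative measures, correlation 0.5 between them, 0.3 with baseline, 0.46 SD, 80% power, two-sided 5%, 15% missing.

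- Variance factor for the baseline-adjusted patient mean: (1 + 3 × 0.5)/4 − 0.3² = 0.625 − 0.09 = 0.535.
- n per group = 2 × 0.535 × (1.96 + 0.84)²/0.46² ≈ 39.7. Dividing by 0.85 gives 46.7, so 47 per group and 94 in total. (Rounding to 40 before inflating gives 48 per group, 96 in total.)
- Power with 47 × 0.85 = 39.95 per group: Φ(0.46 × √(39.95/(2 × 0.535)) − 1.96) = 80.3%.

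The stated 94 and 80% therefore hold with baseline cTnT as the only covariate in the calculation.

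**2. Primary model with a size or age covariate.** Let q be the share of the remaining patient-mean variance that the covariate explains. The documents give no value, so q is an assumption. Replace 0.535 by 0.535 × (1 − q):

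| q | Power | Detectable difference (SD) |
|---|---|---|
| 0 | 80.3% | 0.458 |
| 0.05 | 82.2% | 0.447 |
| 0.10 | 84.2% | 0.435 |
| 0.20 | 88.2% | 0.410 |
| 0.30 | 91.9% | 0.384 |

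**3. Blood loss, by formula.** Assume that loss is proportional to weight, so log loss = log weight + log loss per kg. Let s_w be the log-SD of weight and s_b that of loss per kg. Without weight in the model the residual variance is s_b² + s_w²; with it, s_b². Share of information kept = s_b²/(s_b² + s_w²).

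- s_b = 0.5, s_w = 1.0: 0.25/1.25 = 0.20.
- s_b = 0.7, s_w = 0.6: 0.49/0.85 = 0.58.

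Confidence intervals would then be √(1/0.58) ≈ 1.3 to √(1/0.20) ≈ 2.2 times as wide as they need be. If loss did not depend on weight at all, nothing would be lost.

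**4. Blood loss, by simulation.** Assumed: 47 per arm; log-normal weight with median 8–10 kg and log-SD 0.6–1.0, held within 3–80 kg; coefficient of variation of loss per kg 0.5–0.8; a true 30% reduction. RACHS was not modelled.

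| Analysis | Power across scenarios |
|---|---|
| Raw mL, no weight | 21–52% |
| Raw mL, weight as covariate | 37–83% |
| mL/kg | 58–93% |
| Log mL, log weight as covariate | 67–95% |

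Weight explained about 33–67% of the variance of raw mL.

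**5. Chance imbalance.** For an age group making up 20% of patients (assumed), the 95% range of the difference between arms is 1.96 × √(2 × 0.2 × 0.8/47) ≈ ±16 percentage points.

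**The case against.** The best reply is that a journal article condenses the full protocol. It never says that blood loss is analysed as raw volume, and units, indexing and transformation are commonly left to the analysis plan. That stands. A reader might infer that blood loss will be swamped by body size, but this needs both unindexed analysis and a real dependence on size, and the article establishes neither. If the unseen plan uses mL/kg, most of the blood-loss loss disappears. What remains is the covariate rule itself, which the article does state. A plan that follows it has no size or age term, and one that adds such a term should be reconciled with the published rule.

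Second, adjusting for baseline and the stratification factor is a standard choice, and it delivers the planned power. That also stands. A reader might infer that the primary model certainly gives up precision or that 94 is too few. The documents support neither: they report no association of age or weight with cTnT, and baseline cTnT and RACHS may already carry part of any such association. The gain may be zero.

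Third, a reader might take possible imbalance in age for bias. Randomisation protects the comparison, and the confidence interval already allows for chance imbalance.

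Finally, it is tempting to ask for the covariate in every secondary model. Nothing in the article shows that intubation time or fitness for transfer depends on size, and in a survival model a prognostic covariate changes the hazard ratio being estimated.

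**Conclusion.** The point holds as one of efficiency. The stated covariate rule contains no measure of size or age for a population from birth to 18 years, although both are available at no cost. For 12-hour blood loss, only 20–58% of the information would be kept. That range depends on loss being proportional to weight, on unindexed analysis and on the assumed log-SDs, none of which the documents give. For the primary outcome the possible gain runs from nothing to about 12 power points (80% to 92%) over an assumed 0–30% of variance explained. Neither the validity of the comparison nor the sample size is in question.

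**What to change.** Before unblinding:

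- Add log(weight), or age, to the covariate rule for quantitative outcomes expected to depend on body size, and name those outcomes.
- State the blood-loss measure. Log mL with log weight as covariate had the highest power in the simulation; mL/kg is a simpler alternative.
- Add the same covariate to the primary cTnT mixed model, beside baseline cTnT and the RACHS stratum.
- Treat time-to-event outcomes as optional. If the covariate is used there, say that the hazard ratio is conditional on it.

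If the analysis plan already does this, the article's rule only needs to be reconciled with it. The cost is wording and one degree of freedom per model. No new data are needed, and the sample size does not change.
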